# Sequential choice vs colonoscopy outreach for colorectal cancer screening: Design and rationale of a pragmatic randomized clinical trial

**DOI:** 10.1016/j.cct.2025.108188

**Published:** 2025-12-16

**Keywords:** Colorectal cancer screening, Colonoscopy, Fecal immunochemical test, Nudge, Electronic health record, Behavioral economics

## Abstract

**Background::**

Colorectal cancer (CRC) screening rates remain limited, and effective methods for offering the choice of colonoscopy or stool testing through outreach have not been identified. We evaluate the effect of sequential choice compared to colonoscopy outreach on screening completion, and further evaluate behavioral nudges in the electronic health record (EHR).

**Methods::**

In this pragmatic randomized clinical trial, patients were randomly allocated in a 1:2:2 ratio to 1) usual care (no outreach), 2) colonoscopy only, or 3) sequential choice of colonoscopy, then fecal immunochemical testing (FIT). Patients in arms 2 and 3 were additionally randomized to receive either (a) usual care, or (b) a visit-based, clinician-directed nudge facilitated by the EHR with follow-up texting to the patient. The primary outcome is CRC screening completion within 3 years by either colonoscopy, 2 negative fecal immunochemical tests (FIT), or 1 positive FIT followed by colonoscopy within one year.

**Analysis::**

For the patient-directed analysis, the primary outcome will be evaluated by comparing CRC screening completion among patients randomized to either outreach arm (2 or 3) to the no outreach arm (1). We will also compare completion between the colonoscopy only arm (1) and the sequential choice arm (2). For the visit-based analysis, we will compare CRC screening completion among patients between the usual care arms (2a and 3a) and the nudge arms (2b and 3b).

**Conclusion::**

This trial is unique in evaluating the long-term effectiveness of offering sequential choice to colonoscopy alone through a multi-level, centralized outreach and visit-based design.

**Clinical Trials Identifier::**

NCT05693649

## Introduction

1.

Colorectal cancer (CRC) is the second leading cause of cancer death in the United States (US). Routine screening has reduced the burden of disease, but national screening still falls below goals, with rates at approximately 67 %. [1–5] There are also persistent racial, ethnic and socioeconomic disparities in outcomes, particularly among Black patients. [6,7] Multi-level approaches that decrease clinician and patient barriers are important for durably increasing screening rates, including both direct population-based outreach along with clinician recommendations during visits. [8] However, these approach have not been adopted widely and have been difficult to sustain over time.

New insights from behavioral science have helped recognize that humans use systematic shortcuts in thinking that thwart long-term health goals. [9–11] For example, present-time bias reduces the motivation to engage in behaviors whose outcomes are not immediate; status quo bias makes past choices the more likely future choices; and choice overload paralyzes decision making, even when stakes are high. [12–14] However, there is evidence that we can harness these same biases to encourage healthy behaviors. [15,16] Reminders can overcome present-time bias; shifting from opt-in to opt-out framing can increase participating in cancer screening; and both can simplify decisions and prevent overload. [17–21]

Colonoscopy and fecal immunochemical testing (FIT) are evidence-based and top-tier tests for CRC screening. [4,22] FIT achieves a higher response rate in a single outreach, but it requires annual adherence. [23,24] Colonoscopy is more sensitive for identifying polyps and cancer, but the procedure is costly and burdensome for patients. [8] There is evidence that offering a choice of testing can boost screening rates, but there is the potential for choice overload. [25,26] Sequential choice that offers colonoscopy first, then FIT to those who decline or defer has the potential to simplify choice, and it is recommended by clinical guidelines, but there is limited evidence to support this approach. [27–29]

This trial evaluates a multi-level screening intervention that combines direct outreach and nudges in the electronic health record (EHR) during visits to durably increase screening rates. We incorporate behavioral principles such as opt-out framing and reminders while evaluating the comparative effectiveness of sequential choice compared to colonoscopy only.

## Methods

2.

The aims of the 3-year trial are to evaluate the rates of CRC screening completion between patients with 1) no outreach, 2) colonoscopy only, or 3) sequential choice (colonoscopy, then FIT); and to compare the effect of EHR nudges to clinicians and patients during office visits. The trial was approved by the University of Pennsylvania Institutional Review Board and a waiver of consent was granted. [30] It was prospectively registered on clinicaltrials.gov (NCT05693649).

### Setting

2.1.

The trial is being conducted over approximately 3.5 years (June 2023 and January 2027) in 24 primary care clinics within a large, urban, academic health system in the Philadelphia region.

### Eligibility and enrollment

2.2.

Using automated data extraction from the EHR database (Epic Clarity), we identified eligible patients at participating primary care practices within 30 miles of a health system endoscopy site. [31] We included patients aged 50–72 who, at the time of enrollment, were seen by primary care at least once in the past two years, were of average risk of developing CRC, and who were not up-to-date with CRC screening per guidelines at the time. [32] Patients who were not average risk were excluded, including those with a personal or significant family history of CRC, colonic polyps, Hereditary Nonpolyposis Colorectal Cancer Syndrome (HNPCC/Lynch Syndrome), other gastrointestinal cancer, gastrointestinal bleeding, or inflammatory bowel disease (Supplement Table 1). Additionally, patients who may not benefit from screening were excluded, including those with dementia, metastatic cancer, para/quadriplegia, total colectomy, those receiving hospice or palliative care, or those with an elevated chance of mortality within 3 years (Supplement Table 2). Finally, patients were also excluded if they were uninsured, had an active order for FIT (within the last 60 days) or multitarget stool DNA testing (MT-sDNA), or a positive stool test (FIT or MT-sDNA) result in the last 5 years.

We developed a mortality risk indicator to exclude patients who may not benefit from screening. Existing risk indicators included variables such as insurance type that may differentially exclude patients who are already underrepresented in screening but still might benefit. [33,34] Our model uses predictive factors related to end-of-life risk, from domains similar to those represented in the Epic End of Life (EOL) Care Index, with the Medicaid predictor removed, and additional medication, diagnosis, and utilization variables added (Supplement Table 3). This 3-year mortality prediction model was trained on a cohort of 42,451 patients eligible for CRC screening as of 12/1/17, 12/1/18, and 12/1/19 (three years, used to mimic the length of the intervention) using weighted logistic regression with L1 regularization and 5-fold cross validation, which was implemented via LogisticRegressionCV from the scikit-learn library (v1.0.2) in Python. [35] Of this cohort, 779 (1.8 %) patients were deceased within 3 years. The AUC of this prediction model was 0.844 in the held-out test set, performing similarly to the Epic EOL model (0.838). Using a threshold of 0.9, the model’s accuracy was 97.2 % with a positive predictive value of 26.8 %. Upon completion of enrollment, 625 patients of 19,969 eligible patients (3.1 %) were excluded because of an increased risk for mortality within three years.

### Randomization

2.3.

In each of four batches, 5000 eligible patients were randomly selected from the approximately 20,000 eligible patients identified. Patients were individually randomized, stratified by practice, to three arms related to outreach in a 1:2:2 ratio to no outreach (arm 1), colonoscopy only (arm 2), or sequential choice of colonoscopy then FIT (arm 3). In the outreach arms 2 and 3, patients were additionally randomized to receive either (a) no additional intervention, or (b) a visit-based, clinician-directed nudge facilitated by the EHR and follow-up text messaging (Fig. 1). Upon completion of enrollment, 19,344 patients were randomized as follows: arm 1 (no outreach): 3877; arm 2a (colonoscopy only, no nudge): 3865; arm 2b (colonoscopy + visit nudge): 3870; arm 3a (sequential choice): 3867; arm 3b (sequential choice + visit nudge): 3865. See Table 1 for participant characteristics by study arm. Randomization was implemented using block randomization with stratification using Way to Health (W2H), an NIH-funded software platform that automates research and outreach for patient engagement. [36]

### Interventions

2.4.

All patients randomized to an outreach arm (arms 2 and 3) receive centralized direct outreach to complete colonoscopy. Regional physician leads sign bulk order colonoscopy for eligible patients, while the primary care provider (PCP) is listed as the authorizing provider. Patients receive outreach via the electronic patient portal (if active status) or mailed letter informing them their PCP has ordered the procedure, including the colonoscopy order (mailed only) and providing the phone number for direct access to colonoscopy. Outreach is conducted in batches of approximately 4000 patients every 2 months to minimize the burden on clinical services. Additionally, at the time of initial outreach, all patients in arms 2 and 3 receive a text message from the PCP or practice indicating that their primary care provider has already ordered a colonoscopy, with scheduling information. Text messaging via the Way to Health platform is bidirectional, offering automated replies to common colonoscopy related questions. If text messaging is not available, the patient receives similar messaging using Automated Voice Recording (AVR).

Patients who are not up-to-date on screened based on EHR data (Epic Health Maintenance), do not schedule their colonoscopy within 2 months from initial outreach, and have not been ordered for multitarget stool DNA (MT-sDNA) receive an additional mailed and text message reminder. Those in arm 2 (colonoscopy only) receive a mailed reminder about colonoscopy scheduling. In arm 3 (sequential choice), patients receive a mailed FIT kit with instructions, a pre-paid return envelope and a letter describing the stool test as an annual alternative to colonoscopy. The FIT order is signed in bulk by the regional physician lead, with results going back to the PCP as the authorizing provider.

Patients in arms 2 and 3 who have still not completed FIT, or either scheduled or completed colonoscopy at 4 months, receive a final text message reflecting their study arm assignment recommendation. This centralized, direct patient outreach is repeated annually for patients who are not up-to-date on CRC screening, in the same 4 batches of the prior study year.

Patients randomized to a visit-based nudge arm (2B or 3B) who attend a visit with their PCP additionally receive a visit-based, clinician-directed nudge and a follow-up text 3 days post-visit. The nudges include an EHR static highlighted notification (Epic storyboard banner)(Fig. 2) notifying clinical staff (medical assistants, PCPs, and nursing staff) that a colonoscopy and/or FIT order has been placed on their behalf and encouraging discussion around completion. Patients receive a follow-up text message 3 days after the visit reminding them to follow through on active CRC screening orders (colonoscopy, FIT, or both).

Participants randomized to arm 1 (usual care) do not receive any direct outreach or visit-based nudges from this trial. Fig. 1 summarizes the trial design.

As per usual care across the health system, endoscopy reports and follow-up recommendations are provided to patients by the performing gastroenterologist, and patients completing FIT are also be notified of their results. If a FIT positive patient does not schedule diagnostic colonoscopy follow-up within two months of their result and has not received standard follow-up outreach from the practice, the research team sends a note in the EHR to population health coordinators who will provide additional support.

We will obtain baseline data from the EHR on demographics, prior CRC screening, co-morbidities, and mortality risk from automated data extraction and free text searches, as needed. We will use chart review to track outcomes of colonoscopies that are performed with polypectomy, so that we can categorize the finding. Study data are being collected and managed using REDCap electronic data capture tools hosted at the University of Pennsylvania. [37,38]

Changes in Health Maintenance (HM) status are assessed via daily Clarity query to identify documentation of screening results and determine continued outreach. All HM status changes and results (internal or external) picked up by this query are chart-reviewed and only counted toward an outcome if documentation is present in the patient chart.

### Mixed methods evaluation

2.5.

Annually, upon completion of all direct outreach in Batch 3, we send a validated survey guided by the Preventive Health Model (PHM), a selfregulation model shown to predict colorectal screening behaviors in a diverse population, to a select group of enrolled participants. [39,40] The original survey was developed and refined by Vernon and colleagues in 1997 and further validated in a larger and more diverse population by Tiro and colleagues in 2005. [40,41] For a target sample size of 100 completed surveys per year (300 total), and assuming a 20 % response rate, we are randomly selecting a minimum of 500 patients each year, stratified by race (Black patients vs all others) and study arms (intervention arms only) to complete the survey.

The survey consists of 16 individual items spanning five psychosocial constructs: 1) salience and coherence, 2) social influence, 3) cancer worries, 4) perceived susceptibility, and 5) response efficacy. It will also include questions about CRC screening exposure and preferences. Patients randomly selected to complete the survey receive an invite via text message (Way to Health), and participants receive up to 2 automated reminders at 4 and 9 days. If our sample is lower than expected, remaining participants are purposively selected in batches of 10 to receive a manually generated text message offering a scheduled date and time to complete the survey by phone until an appropriate sample is obtained. Survey administration is repeated in Years 2 and 3, with no repeated participants in subsequent years. We monitor responses by study arm, race, and sex to ensure a representative sample.

In year 3 of the trial, a purposive sample of 60 patients will be contacted by phone to conduct qualitative interviews to understand their experience with the specific outreach strategy and the reasons for the effectiveness (or lack of effectiveness) of each intervention. Guided by domains with the PHM, we will also ask semi-structured questions about their perception of the impact and design of outreach.

We will also conduct qualitative interviews with 15 clinicians in the visit-based nudge arms to better understand their experiences with the interventions. Interview participants (patients and clinicians) will be consented and given a $25 gift card in appreciation of their time.

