### Mixed methods analysis

3.4.

The annual embedded survey consists of 16 individual items spanning five psychosocial constructs: 1) salience and coherence, 2) social influence, 3) cancer worries, 4) perceived susceptibility, and 5) response efficacy. [39,40] Each construct can be summed to create a score within each construct, and in total related to beliefs about CRC screening. We will calculate mean differences within each of the five constructs, evaluate each construct on its own scale, and overall look for any associations between CRC screening completion at 3 years and screening beliefs. Finally, we’ll compare screening exposure and preference responses to the type of screening completed at 3 years, if any. We will compare outcomes for those offered the survey and those who were not, to see if receiving the survey was associated with cancer screening completion.

For analysis of the qualitative interview transcripts, two members of the research team will independently review the transcripts for inductive themes through an iterative process using the constant comparative approach. [44–46] After the study team reviews five sets of transcripts, we will develop a coding scheme that will be applied to subsequent data and modified as the study progresses and new themes emerge. The study team members will assess and reassess our inter-rater reliability.

Finally, we will perform a cost analysis using resource utilization to determine the incremental cost of outreach in each arm and the incremental cost of additional patients screened to evaluate resource requirements for scale. We will evaluate the cost from the perspective of the health system, including the time spent by staff that would be needed as part of routine operations when implemented, while not including effort for activities that are only part of the research process.

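### A shortfall in the randomly drawn survey sample is made up by purposive selection for a phone survey, so the topped-up respondents differ from the rest in both how they were chosen and how they were contacted

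*Protocol article*

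**What the plan says.** Protocol article, section 2.5 (Mixed methods evaluation), sets the survey target and the draw: "For a target sample size of 100 completed surveys per year (300 total), and assuming a 20 % response rate", followed by "we are randomly selecting a minimum of 500 patients each year, stratified by race (Black patients vs all others) and study arms", with intervention arms only. Those drawn are invited by text and get up to two automated reminders.

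The same section then gives the rule for a shortfall: "remaining participants are purposively selected in batches of 10 to receive a manually generated text message" that offers an appointment to do the survey by phone, continuing until the sample is judged appropriate. No criterion for the purposive choice is given. The balancing statement is: "We monitor responses by study arm, race, and sex to ensure a representative sample".

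Section 3.4 (Mixed methods analysis) uses the survey quantitatively. It plans mean differences within the five constructs, will "look for any associations between CRC screening completion at 3 years and screening beliefs", and sets stated preferences against the type of test completed. It also compares outcomes between patients offered the survey and patients not offered it. It does not mention sampling stage or survey mode.

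**The concern.** The design begins as a probability sample and, on a shortfall, continues as a judgement sample. Two things change at the same step: the way a patient is picked, and the way the patient is contacted and surveyed. Watching arm, race and sex can balance those three margins, but it does not make selection random among patients who share them. Screening beliefs vary within such cells, and beliefs are what the survey measures.

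Three planned uses are exposed.

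- **Construct scores** can shift if topped-up respondents hold different beliefs, or answer differently by phone.
- **Associations between beliefs and 3-year completion** can be distorted if selection or mode is related to both.
- **The offered versus not-offered comparison** draws its strength from random selection of who is offered the survey. It loses part of that if purposively chosen patients from outside the draw count as offered.

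This is a rule the article states, not a detail left to a fuller document.

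**Working it through.** **Inputs from section 2.5.** Target T = 100 completes per year; assumed response r = 0.20; minimum random draw n = 500 per year.

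**Reproducing the plan's figure.** n = T / r = 100 / 0.20 = 500. This matches the stated minimum, so at that minimum the expected yield equals the target, with no reserve.

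**How often the top-up would be triggered.** Let X ~ Binomial(500, r), treating responses as independent. A shortfall is X < 100. Only r = 20% comes from the article; the other rates are assumptions to show a range.

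| Response rate | Expected completes (500 × r) | P(X < 100) | Expected top-up share of 100, (100 − 500r)/100 |
|---|---|---|---|
| 22% | 110 | 13% | 0 |
| 20% (plan) | 100 | 48% | 0 |
| 18% | 90 | 87% | 10% |
| 15% | 75 | above 99% | 25% |
| 10% | 50 | above 99% | 50% |
| 5% | 25 | above 99% | 75% |

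At the plan's own 20%, and with years treated as independent, the chance of at least one shortfall in three rounds is 1 − (1 − 0.482)³ ≈ 0.86. Those shortfalls would usually be small: the standard deviation of X is √(500 × 0.2 × 0.8) ≈ 8.9 completes.

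The article says a minimum of 500, so a larger draw is already allowed. At 20% response, 558 random invitees give a 90% chance of at least 100 completes.

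**How far a mean score could move.** Shift = top-up share × difference between topped-up and first-stage respondents. The article gives no such difference; 0.3 SD is an assumption for illustration.

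- Share 10%: 0.10 × 0.3 = 0.03 SD
- Share 25%: 0.25 × 0.3 = 0.075 SD
- Share 50%: 0.50 × 0.3 = 0.15 SD

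The standard error of a mean at 100 completes is 1/√100 = 0.10 SD. On these assumptions the shift exceeds one standard error only when the share is above one third (0.10 / 0.3).

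**Why adjustment cannot separate the two causes.** Phone administration is described only for the top-up. If first-stage patients complete the survey without an interviewer, as the text invitation implies but does not state, the mode indicator and the stage indicator are the same variable. Its coefficient is then the sum of a mode effect and a selection effect.

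**Two readings of who is added.**

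| Added patients are | Patients approached | Completed sample | Offered vs not offered |
|---|---|---|---|
| Non-responders in the random draw | All randomly drawn | Part chosen by judgement, other mode | Random basis kept |
| New patients outside the draw | Part chosen by judgement | Part chosen by judgement, other mode | Random basis weakened |

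The problem with the completed sample appears under both readings. The problem with the last comparison appears only under the second.

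**The case against.** The strongest reply is that the added patients may simply be those in the random draw who have not answered. Everyone approached would then have been randomly selected, and the step would be phone follow-up of non-responders, which is ordinary practice and may improve coverage. The wording allows this. It narrows the point, because the offered group would stay random, but it does not remove it: which non-responders get the phone offer is still a judgement.

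Second, at 20% response about 80% of invitees do not answer, so the completed sample is self-selected before any top-up. Steering contacts to thin arm, race or sex cells could make it more representative. This stands. Random order within those cells keeps that benefit.

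Third, the illustration concerns a mean. A common mode offset cancels in a difference between groups with similar phone shares, and it biases an association with completion only if it is related to completion. This also stands, and it is why no bias figure is claimed.

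A reader might infer more than the documents support:

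- **That the survey as a whole loses its random basis.** First-stage respondents still come from a random draw and can be analysed separately if they are flagged.
- **That staff choose patients knowing their screening status.** Section 2.4 describes a daily query of that status for outreach and outcomes, but nothing links it to survey selection.
- **That section 3.4 prescribes pooling the two stages.** It is silent on this.
- **That the aim of a representative sample fails.** That is not shown.

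**Conclusion.** The point holds as a minor one about an ancillary survey. The stated rule brings judgement-based selection and a different contact mode together into a sample that is otherwise randomly drawn. This can bias the construct scores and the belief-completion associations and, under one reading, the offered versus not-offered comparison.

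The rule would probably be used: the chance of a shortfall is about 48% per year with exactly 500 invitees at the planned response rate, and higher if response is lower. At the planned rate few respondents would be affected. A substantial share needs response nearer 10% to 15%, which is an assumption. The size and direction of any bias cannot be derived from the article.

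The survey is not among the primary or secondary outcomes in section 3.1, so the trial's main conclusions do not depend on this.

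**What to change.** For survey rounds still to come:

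1. State in section 2.5 whether the added participants are non-responders in the random draw or new patients.
2. Contact them in random order within the same race-by-arm strata, or within under-represented arm, race or sex cells. The batches of 10 and the phone offer can stay.
3. Record sampling stage and survey mode for each respondent.
4. Report a sensitivity analysis of the section 3.4 results restricted to respondents from the initial random text stage. A mode covariate alone is not enough, because it cannot separate mode from selection.
5. In the offered versus not-offered comparison, define offered as the randomly drawn patients only.

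For rounds already fielded, stage and mode can be flagged afterwards where contact records allow, so that the restricted analysis covers them too. Purposive sampling can remain for the qualitative interviews.

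The cost is small: an ordered contact list and two recorded variables. A few more contacts may be needed to reach 100, and the selection rule would differ from that of earlier rounds, which the report should say.
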